#### Follow-up

At the 6-month follow-up, the research assistant will collect ECBI, SCS, and FQ and a quantitative/qualitative follow-up questionnaire. This questionnaire includes Likert-type scales and opportunities for written feedback to assess levels of engagement, helpful aspects of the trial, level of competency with implementing IYP strategies, and changes in relationships and behaviour noticed by parent/carers (Table 1).

**Table 1 T1:** Summary schedule of data collected

**Method of data collection**	**Screening**	**Baseline**	**Post-intervention**	**6-month follow-up**
ECBI & SCS*	**X**		**X**	**X**
Demographics		**X**		
FQ		**X**	**X**	**X**
PSQ			**X**	
Follow-up Questionnaire				**X**

ECBI, Eyberg Child Behavior Inventory; FQ, Family Questionnaire; PSQ, Parent Satisfaction Questionnaire; SCS, Social Competency Scale. *Screening is within 3 weeks of baseline data collection.

### Sample size

Previous research indicated that 80% of participants receiving HPS completed the IYP group [43,45]. Therefore, a total sample of 126 participants will be collected in order to achieve 50 participants in each treatment arm at post-treatment. This trial represents the first formal assessment of the HPS intervention and is being undertaken as a pilot study to assess the feasibility of a full randomised controlled trial in the wider clinical setting and to collect data to inform the power calculations for such a study. Thus, there is no formal power calculation for the proposed sample size of 126, but this represents a substantial and adequate number of participants representative of those likely to benefit from the intervention. Standard power calculations with 50 in each arm will have 80% power to detect an effect size of 0.57 between the control and experimental group (i.e., Cohen’s *d* = 0.57).

### Randomisation and sequence generation

On completion of baseline data collection, participants will be allocated an identification number and randomised to IYP plus HPS or to IYP alone. An independent statistician using a computer generated randomisation sequence generated prior to the enrolment of any participants will undertake the randomisation. Randomisation will be stratified on each IYP group so that each intake or source group will have approximately equal numbers allocated to each treatment. The randomisation sequence will allocate in a 1:1 ratio to the two treatments arranged in permuted blocks and will be stratified on age (under 5 years and over 5 years), sex, and ethnicity (Maori and Non-Maori). After a participant has met all inclusion criteria and signed informed consent they will be allocated the next available randomisation allocation.

### Allocation concealment

The randomisation list will not be available to any researchers directly involved in the assessment or screening of participants. The participant will only be allocated once all inclusion criteria are met. Following randomisation, participant allocation will be returned to the primary investigator who will inform participants of their allocation and arrange for HPS to begin in the treatment group.

### Blinding

Due to the nature of the study, it is not possible to have a completely blinded design. Participants will know which intervention they are receiving. IYP group leaders will also know who is in the treatment arm as their contribution is a part of the HPS intervention. The primary investigator leads the IYSS team and conducts the multidisciplinary team review and will therefore be aware of those participants in the treatment arm. However, the research assistant undertaking the assessments will be blind and remain blind to treatment allocation throughout the study. Participants will be asked not to reveal the intervention they are receiving to the research assistant. All participants will be given an identification number to ensure the researcher and all those involved in summarising and inputting the data are unaware of the treatment allocation.

### Statistical methods

Standard descriptive statistics will be used to report demographics, baseline status for outcome measures, and presentation features for the sample as a whole and by randomly allocated group. These will include means, medians, ranges, and standard deviations for metric measures, and frequencies and percentages for categorical measures.

The primary outcome measure, the change in the parent scores on the ECBI total problem score from pre- to post-intervention will be calculated for each individual and will be compared between randomised groups using ANOVA with randomised group and strata as fixed factors. Additional sensitivity analyses will be undertaken using an ANCOVA model and including the baseline level of the change score as a covariate.

The metric secondary outcome measures that assess change from pre- to post-intervention in SCS, and child behaviour, parenting practices, parent relationships and parental wellbeing as measured by the FQ, will also be compared between randomised groups using ANCOVA models with baseline levels as covariates and randomised group and strata as fixed factors.

The categorical outcomes at post-treatment including the percentage of parent scores on the ECBI and the SCS that are in the normal range at post-treatment and the percentage of participants with at least 80% engagement in IYP will be compared between randomised groups using χ^2^ tests.

As outlined above, the stratification factors will be included as factors in the ANCOVA models analysing the primary and secondary continuous outcomes and, depending on sample size, may also be included in a Mantel-Haenszel χ^2^ analysis of the post-treatment categorical outcomes.

The maintenance of post-treatment results for the primary and secondary outcomes at six months post-intervention will be compared between randomised groups using ANOVA. This analysis will explore change in the metric measures from immediately post-treatment to six months between the two randomised groups.

Additional exploratory analyses including correlation coefficients and further ANCOVA and logistic regression models may be used to identify the characteristics of subsets of participants who respond particularly well or poorly to the addition of HPS to IYP.

A two tailed α = 0.05 will be used for all statistical testing of the results of the above analyses and results will be summarised using 95% confidence intervals of the differences between randomised groups. Should any of the above metric outcome measures not meet requisite assumptions for parametric analyses after transformation, non-parametric tests, including the Mann-Whitney U-test, will be used for analyses.

All participants’ data will be included in the intention-to-treat analysis. Considerable efforts will be made to obtain post-treatment and follow-up data from all randomised participants even if they do not complete the treatments. Missing data will in the first instance be managed with a ‘last observation carried forward’ approach with additional sensitivity analyses undertaken using multiple imputation methods. The extent of compliance, including information on those who do not complete either HPS or IYP, will be captured and summarised. A per-protocol analysis, including only those who complete the treatments without protocol violations and have all relevant assessments at each time, will also be undertaken to identify whether compliance factors affect outcomes.

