### Outcomes

#### Primary outcome

The primary outcome is a change in child behaviour from baseline to post-intervention in the parent-reported ECBI Problem scale.

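### The primary ECBI Problem analysis leaves the baseline score out of the model and gains nothing by it; a baseline-adjusted ANCOVA should be named as the single primary model

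*Protocol article*

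**What the plan says.** The Primary outcome section reads: "The primary outcome is a change in child behaviour from baseline to post-intervention in the parent-reported ECBI Problem scale". Statistical methods then assigns the models.

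- **Primary outcome.** Individual change scores "will be compared between randomised groups using ANOVA with randomised group and strata as fixed factors". Baseline is not in this model.
- **Sensitivity analysis of the primary outcome.** "Additional sensitivity analyses will be undertaken using an ANCOVA model and including the baseline level of the change score as a covariate".
- **Metric secondary outcomes, pre to post.** These are compared "using ANCOVA models with baseline levels as covariates and randomised group and strata as fixed factors".
- **Later cross-reference.** It says that "the stratification factors will be included as factors in the ANCOVA models analysing the primary and secondary continuous outcomes".
- **Fallback.** If a metric outcome still fails parametric assumptions after transformation, "non-parametric tests, including the Mann-Whitney U-test, will be used for analyses". The article gives no criterion for failure.

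Missing data are handled first by last observation carried forward (LOCF), with multiple imputation as sensitivity. Table 1 shows the ECBI collected once before treatment, at screening. A participant without a post-treatment score therefore gets a change of exactly zero.

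**The concern.** The one primary outcome gets a less precise model than the secondary outcomes, and no reason is given. The baseline ECBI Problem score is already collected, so leaving it out saves nothing. A chance baseline difference between arms also carries into the change-score estimate, where ANCOVA would adjust for it.

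Two further points concern pre-specification. The cross-reference mentions ANCOVA models for the primary outcome without saying that it means the sensitivity analysis, so a reader cannot be sure which model is primary. The fallback lets the data decide whether the primary result comes from a linear model or a rank test, and LOCF zeros make non-normal residuals likely.

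Precision matters even in a pilot. The Sample size section says the trial is to supply data for the power calculations of a full trial. The Discussion would read a small effect as possible lack of added benefit and expects the findings to inform national policy.

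**Working it through.** **The plan's own figure.** With 50 per arm, d = 0.57 and two-sided α = 0.05, the noncentrality is 0.57 × √(50/2) = 2.85. Power is 80.6% by the noncentral t and 81.3% by the normal approximation. The stated 80% reproduces.

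**Inputs not in the documents.** The baseline-to-post correlation ρ and the SD ratio k = SDpre/SDpost are assumptions. I use ρ = 0.3, 0.5 and 0.7.

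**Complete data.** In units of the post-treatment SD:

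- variance of change = k² + 1 − 2ρk
- ANCOVA residual variance = 1 − ρ²
- ratio = (1 − ρ²)/(k² + 1 − 2ρk)

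The denominator exceeds the numerator by (k − ρ)². The ratio therefore never exceeds 1, and equals 1 only when ρ = k. With k = 1 it reduces to (1 + ρ)/2.

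| ρ | ratio, k = 1 | ratio, k = 0.7 | ANCOVA n per arm matching 50 (k = 1) | ANCOVA power (k = 1) |
|---|---|---|---|---|
| 0.3 | 0.65 | 0.85 | 32.5 | 93.8% |
| 0.5 | 0.75 | 0.95 | 37.5 | 90.2% |
| 0.7 | 0.85 | 1.00 | 42.5 | 86.4% |

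The power column takes d = 0.57 in change-score SD units, 50 completers per arm and 90 error degrees of freedom. For ρ = 0.3 the noncentrality is 2.85/√0.65 = 3.53.

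**Under the planned LOCF.** Let a fraction m = 0.20 be missing at random with change set to zero, k = 1, and mean change μ in SD units. The 20% follows from the 80% completion figure in the Sample size section.

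- variance of change = (1 − m) × 2(1 − ρ) + m(1 − m)μ²
- part explained by baseline = [(1 − m)(1 − ρ)]²
- ratio = 1 − explained part / variance

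| ρ | variance, μ = 1 | explained | ratio, μ = 1 | ratio, μ = 2 |
|---|---|---|---|---|
| 0.3 | 0.8 × 1.4 + 0.16 = 1.28 | 0.3136 | 0.755 | 0.82 |
| 0.5 | 0.8 × 1.0 + 0.16 = 0.96 | 0.1600 | 0.83 | 0.89 |
| 0.7 | 0.8 × 0.6 + 0.16 = 0.64 | 0.0576 | 0.91 | 0.95 |

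At μ = 1 the gain is worth about 32%, 20% or 10% more participants (1/ratio − 1). At μ = 2 it is worth about 22%, 12% or 5%.

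**The fallback.** I simulated 63 per arm with 20% LOCF zeros, ρ of 0.3 to 0.7, mean change of 0.5 to 2 SD, and a treatment effect of zero or 0.57 change-score SDs. A Shapiro-Wilk test on the residuals of the change-score model rejected in about 64% to over 99% of trials. The plan does not name that test; it serves here only as a gauge of non-normality.

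With complete normal data and 50 per arm, simulated power was 78–79% for Mann-Whitney on change scores, 80–81% for the unadjusted change-score comparison, and 86–94% for ANCOVA. Type I error was about 5% for each test taken singly.

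**The case against.** The best defence is that nothing here is invalid. The outcome is defined as change and the primary test matches it. Under randomisation that test is unbiased and holds its error rate. A chance baseline imbalance would show in the planned sensitivity ANCOVA. The trial is a pilot that disclaims a formal power calculation. All of this stands, and it limits the severity.

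Several stronger readings are tempting, but the documents do not support them.

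- **That the plan names two primary models.** The cross-reference concerns the stratification factors and can be read as covering the sensitivity ANCOVA already named for the primary outcome. It is ambiguous, not contradictory.
- **That the primary model is open to choice after the data are seen.** ANOVA is pre-specified as primary and ANCOVA as sensitivity. Only the non-parametric switch depends on the data.
- **That the complete-data gain applies in full.** At k = 1 the first table implies 54%, 33% or 18% more participants. Those figures and the matching power gains leave out the plan's own LOCF rule, under which the gain is smaller.
- **That the fallback must discard strata and baseline.** The wording is inclusive, so an adjusted or stratified rank method is not excluded; Mann-Whitney is only the one test named. Nor are transformations ruled out by zero or negative changes, since a shift or signed transformation can be used. The exact trigger is a detail that an article may leave to the full plan.

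**Conclusion.** The point holds as one of efficiency and clarity. Leaving baseline out of the primary model gives up precision for no benefit. The variance ratio is 0.65 to 0.85 with complete data and equal SDs, and about 0.76 to 0.91 under LOCF with 20% missing and a mean change of 1 SD, for ρ from 0.3 to 0.7. It rises to 1, meaning no gain, when ρ equals the SD ratio. Direction is certain apart from one degree of freedom; size rests on assumed values of ρ, the SD ratio, the missing fraction and the mean change.

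Under normality Mann-Whitney loses only about 1–3 percentage points of power against the planned unadjusted comparison, but about 8–16 against ANCOVA. No stated figure is wrong. This is a recommended free improvement, not a must-fix.

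**What to change.** - Name one primary model: ANCOVA of the post-treatment ECBI Problem score on randomised group, baseline ECBI Problem score and the stratification factors, reported as an adjusted mean difference with 95% confidence interval.
- Report the change-score ANOVA, and any rank-based test, as sensitivity analyses.
- If residuals are non-normal, keep the ANCOVA and use robust or bootstrap standard errors instead of switching tests.
- Reword the later sentence on ANCOVA models so that it agrees with the primary model named.

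The cost is wording only. Baseline is already collected, and a baseline-adjusted ANCOVA of this outcome is already planned.

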#### Secondary outcomes

• The percentage of parent scores on the ECBI that are in the normal range at post-treatment.

• The percentage of parent scores on the Child SCS that are in the normal range at post-treatment.

• Changes from pre- to post-intervention in child behaviour, parenting practices, parent relationships, and parental well-being measured on the Family Questionnaire (FQ) scales.

• The percentage with at least 80% engagement in IYP measured on the attendance register.

• Levels of parent satisfaction with IYP measured using the Parent Satisfaction Questionnaire.

• Maintenance of improvement at 6-month follow-up measured on the FQ, ECBI, and SCS.

• Parent reports of competence with implementing IYP strategies in the home as reported in the Follow-up Questionnaire at 6 months.

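### The planned 6-month maintenance contrast has the same expected value, zero, whether the HPS benefit lasts or never existed, so it does not estimate the HPS effect at 6 months

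*Protocol article*

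**What the plan says.** The Protocol article lists among its secondary outcomes "Maintenance of improvement at 6-month follow-up measured on the FQ, ECBI, and SCS". Under Statistical methods it names the test: "The maintenance of post-treatment results for the primary and secondary outcomes at six months post-intervention will be compared between randomised groups using ANOVA". The next sentence fixes the contrast: "This analysis will explore change in the metric measures from immediately post-treatment to six months between the two randomised groups".

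The other between-arm outcome analyses described there stop at post-treatment. The primary outcome does too: "The primary outcome is a change in child behaviour from baseline to post-intervention in the parent-reported ECBI Problem scale". Metric secondary outcomes at post-treatment are to be analysed by ANCOVA with the baseline level as covariate and the strata as factors.

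On missing data the same section says: "Missing data will in the first instance be managed with a ‘last observation carried forward’ approach". Multiple imputation is added as a sensitivity analysis, and a per-protocol analysis is also planned. On testing: "A two tailed α = 0.05 will be used for all statistical testing of the results of the above analyses", with results summarised by 95% confidence intervals.

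Table 1 shows ECBI and SCS at screening, post-intervention and 6 months, and FQ at baseline, post-intervention and 6 months.

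**The concern.** The 6-month contrast starts from the post-treatment score, which is itself an outcome observed after randomisation. Any HPS effect already present at that visit is subtracted out, and what remains is the part of the effect that appears or disappears afterwards.

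That is a legitimate question, but it is not whether HPS families are better off than control families at 6 months. A result near zero fits a lasting benefit and fits no benefit at all. An HPS arm that has kept half of its advantage produces a contrast against HPS although it is still ahead.

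At stake is the estimate of durability. Followed as written, the plan collects 6-month ECBI, SCS and FQ scores but reports no estimate and no interval for the HPS effect at that visit. The article describes the trial as informing a larger trial and possibly policy, and both uses would need that figure.

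**Working it through.** **Inputs from the Protocol article.** Sample size: 50 per arm at post-treatment, effect size 0.57, 80% power. Statistical methods: two-sided α = 0.05.

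**Assumption.** The article gives no correlation ρ between visits, so a range of 0.5 to 0.8 is used. Scores are scaled to SD 1.

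**1. The plan's own figures.** The article states "Standard power calculations with 50 in each arm will have 80% power to detect an effect size of 0.57" and "a total sample of 126 participants will be collected in order to achieve 50 participants in each treatment arm at post-treatment". With standard error √(2/50) = 0.2, 0.57/0.2 = 2.85 and Φ(2.85 − 1.96) = 81.3%. The noncentral t gives 80.6%, and the detectable effect at 80% power is 0.566. With 80% completion, 50/0.8 = 62.5, so 63 per arm and 126 in total. These figures reproduce. The article states none for the 6-month analysis.

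**2. What the planned contrast estimates.** Let Dpost and D6 be the HPS advantage over control at the two visits. The contrast is D6 − Dpost.
- No benefit at any time: 0 − 0 = 0.
- Benefit of 0.57 fully kept: 0.57 − 0.57 = 0.

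This is algebra and holds for any SD, correlation or effect size.

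**3. Rejection rates.** A change score has SD √(2(1 − ρ)), so the standard error is 0.2 × √(2(1 − ρ)): 0.200, 0.155 and 0.126 for ρ = 0.5, 0.7 and 0.8. The normal approximation with 50 per arm gives the rates below, each listed in that order of ρ.

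| Situation | Dpost | D6 | Planned contrast | Rejection | Baseline-to-6-month contrast | Rejection |
|---|---|---|---|---|---|---|
| Never any benefit | 0 | 0 | 0 | 5 / 5 / 5% | 0 | 5 / 5 / 5% |
| Fully kept | 0.57 | 0.57 | 0 | 5 / 5 / 5% | 0.57 | 81 / 96 / 99.5% |
| Half lost | 0.57 | 0.285 | −0.285 | 30 / 45 / 62% | 0.285 | 30 / 45 / 62% |
| All lost | 0.57 | 0 | −0.57 | 81 / 96 / 99.5% | 0 | 5 / 5 / 5% |

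A simulation of 10,000 trials at ρ = 0.7 agrees. For the planned contrast, the mean difference was −0.001 with 5.4% rejection when there was never a benefit, and −0.002 with 5.0% when the benefit was fully kept.

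The planned analysis therefore separates loss from no loss, and the baseline-referenced one separates an effect from no effect at 6 months. A direct comparison of 6-month levels also does this, with 81% rejection when 0.57 is kept. ANCOVA on baseline has residual variance 1 − ρ². Because 1 − ρ² = (1 − ρ)(1 + ρ), this exceeds neither 2(1 − ρ) nor 1, so ANCOVA is at least as precise as either.

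**4. Carrying the last observation forward.** A family missing at 6 months receives its post-treatment value again, so its change is exactly zero. If a share m is missing equally in both arms and unrelated to the change, the contrast becomes (1 − m)(D6 − Dpost). The article gives no 6-month loss (its 80% concerns completion of the parent group), so m is assumed:
- m = 10%: 0.285 × 0.9 = 0.257
- m = 20%: 0.285 × 0.8 = 0.228
- m = 30%: 0.285 × 0.7 = 0.200

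The shrinkage is the same whether HPS has lost or gained 0.285.

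**The case against.** The strongest reply is that the contrast suits the outcome as worded. Maintenance of post-treatment results can fairly mean whether one arm gives back more than the other, and −0.285 correctly says that HPS lost ground relative to control. The 6-month result will also be read beside the primary result. On one complete data set, the change from baseline to post plus the change from post to 6 months equals the change from baseline to 6 months. The analysis is called exploratory, the trial is a pilot, and the article condenses a fuller protocol.

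Most of this stands, and it limits the point. The two situations can be told apart informally. But adding two point estimates gives no interval, because the two contrasts share the post-treatment score and their covariance is needed. For SCS and FQ the post-treatment analysis is an ANCOVA, so the sum is not exact even for the estimates. The article also does more than leave this open, since it states which contrast the 6-month analysis uses.

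A reader might infer three stronger things that the documents do not support:
- **That a null result will be declared maintenance.** The article states no such rule, and it promises confidence intervals. It also sets no margin, so non-significance would not establish maintenance: with half the benefit lost, the test rejects in only 30% to 62% of trials.
- **That regression to the mean will penalise the arm that improved more.** A true effect between randomised arms does not regress. Only chance imbalance does, and it averages to zero, as the simulation shows.
- **That carrying values forward favours HPS.** It shrinks late gains under HPS as much as late losses, and multiple imputation is planned as a sensitivity analysis.

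**Conclusion.** The point holds in a limited form. The planned 6-month contrast measures relative loss or gain after treatment. Its expectation is zero both under full maintenance and under no benefit at any time, with 5% rejection in each case. It does not itself estimate the HPS effect at 6 months, and the article states no other between-arm comparison of the 6-month ECBI, SCS or FQ scores. The first-line missing-data rule moves this contrast further towards zero in either direction.

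The identity rests on no assumed figure. The rejection rates rest on 50 per arm, equal SDs and ρ between 0.5 and 0.8. The shrinkage figures rest on an assumed share missing, equal in the arms and unrelated to the change.

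The matter affects a secondary outcome and leaves the primary analysis untouched. It should be changed because the remedy is cheap and the missing estimate is the natural summary of durability.

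**What to change.** In Statistical methods, replace the 6-month paragraph so that:
- the main 6-month analysis is the between-arm difference in 6-month scores by ANCOVA, with the pre-treatment score as covariate (screening for ECBI and SCS, baseline for FQ) and randomised group and strata as factors. A mixed model with both follow-up visits and the same adjustment would be equivalent in purpose;
- the difference is reported with its 95% confidence interval;
- missing 6-month data in this analysis are handled by multiple imputation, or by the mixed-model likelihood, rather than by carrying the last observation forward;
- change from post-treatment to 6 months is kept as a descriptive supplement.

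The cost is a few sentences and slightly more analysis work. The data are already scheduled in Table 1, and the ANCOVA form is the one the plan uses for its metric secondary outcomes at post-treatment.

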### Intervention

#### HPS

Participants will receive 10 in-home sessions from a separate therapist accredited in IYP whilst they attend the 14 to 16 week Basic IYP. The intervention will include a comprehensive child assessment, including developmental, medical, and social history, pre-school or school reports, involvement of other agencies, family structure, and parental mental health. Participants will be supported to identify specific goals they wish to achieve and record them. The therapist will visit them in their homes to provide support to personalise and implement the IYP strategies and to address any barriers to implementation of these strategies that they or the therapist identifies. The therapist will follow a structured intervention guide to ensure therapist fidelity. Treatment includes follow-up contact at one-month post-intervention to assess stability of change and provide further assistance if required.

The therapists delivering HPS will meet weekly to review all participants’ progress and identify any additional support required for families. Therapists will have fortnightly contact with IYP group leaders to review attendance and participant progress. Participants will be reviewed monthly by a multidisciplinary team that includes a Child and Adolescent Psychiatrist, Paediatrician, Ministry of Education IYP co-ordinator, and the HPS therapists. Specialist psychiatric and/or paediatric assessment is available if required. This multidisciplinary team will also review any adverse events and assess the likelihood that this may be related to the intervention.

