### Control

Participants will be in the same IYP groups as those in the intervention arm. This is to prevent real or perceived difference between the groups. All IYP groups will be delivered by trained facilitators in CAMHS, the Ministry of Education, or non-government organisations and will receive 2 hours supervision fortnightly. Those in the control will receive the usual support from IYP group leaders and will still have access to all services that would normally be available to them.

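### The per-protocol comparison requires two completed treatments in one arm and one in the other, so it cannot show whether compliance affects outcomes

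*Protocol article*

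**What the plan says.** The Statistical methods section keeps intention-to-treat as the main analysis: all participants' "data will be included in the intention-to-treat analysis". On missing values it says: "Missing data will in the first instance be managed with a ‘last observation carried forward’ approach". Multiple imputation serves as a sensitivity analysis.

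Two compliance items follow. The first is descriptive: "The extent of compliance, including information on those who do not complete either HPS or IYP, will be captured and summarised". The second is a comparison: "A per-protocol analysis, including only those who complete the treatments without protocol violations and have all relevant assessments at each time". The stated purpose is that it "will also be undertaken to identify whether compliance factors affect outcomes".

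What there is to complete differs by arm. For the experimental arm, the HPS section says: "Participants will receive 10 in-home sessions from a separate therapist accredited in IYP whilst they attend the 14 to 16 week Basic IYP". For the other arm, the Control section says: "Those in the control will receive the usual support from IYP group leaders". Controls attend the same IYP groups but are not allocated HPS.

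The article also expects HPS to influence IYP completion. Secondary outcomes lists attendance of at least 80% at IYP, which is compared between arms, and the Discussion hypothesises that HPS will help families stay engaged in IYP.

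**The concern.** Membership of the per-protocol set is decided after randomisation, by a rule that is stricter in one arm. HPS families pass an extra filter, the home sessions. Both arms pass the IYP filter, but allocation is expected to change how many get through it. The families kept in the two arms can therefore differ in motivation or circumstances even if HPS does nothing.

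The set also cannot answer the question given to it. It contains only compliers, so compliance does not vary within it. Its difference from the intention-to-treat result mixes adherence, selection, restriction to complete cases and the removal of carried-forward values.

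What is at stake is interpretation. A per-protocol estimate above the intention-to-treat one invites the conclusion that HPS works when families take it up. One below it invites the opposite. Selection alone can produce either.

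**Working it through.** **The article's own figures (Sample size).** 50 / 0.80 = 62.5, rounded up to 63 per arm, gives 126. With 50 per arm, d = 0.57 and two-sided α = 0.05, power is 81% (normal approximation) or 80.6% (t-test), against 80% stated. Both figures reproduce, and the point contests neither.

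**Inputs**
- IYP completion of 80% (Sample size). This figure comes from families receiving HPS. No control rate is given, so equality between arms is assumed.
- HPS retention of 92% (Background, unpublished open trial). It is taken here as HPS completion among IYP completers, independent of IYP completion. Both are assumptions.
- Correlation ρ between a latent engagement trait and improvement in ECBI: not in the document; 0.3 to 0.5 assumed.
- No true effect of HPS.

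**Formula.** If the most engaged share p of an arm is kept, the mean of a standard normal trait among those kept is m(p) = φ(z)/p, with z = Φ⁻¹(1 − p). The spurious effect is ρ × [m(p in HPS arm) − m(p in control arm)]. A positive value favours HPS.

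**Document rates.** HPS arm 0.80 × 0.92 = 0.736 kept; control 0.80 kept.

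| Scenario | Kept, HPS | Kept, control | m, HPS | m, control | Difference | ρ = 0.3 | ρ = 0.5 |
|---|---|---|---|---|---|---|---|
| Document rates | 0.736 | 0.80 | 0.444 | 0.350 | 0.094 | +0.03 | +0.05 |
| Lower HPS completion (assumed) | 0.65 | 0.80 | 0.570 | 0.350 | 0.220 | +0.07 | +0.11 |
| Lower still (assumed) | 0.55 | 0.80 | 0.720 | 0.350 | 0.370 | +0.11 | +0.19 |
| HPS raises IYP completion, no extra HPS filter (assumed) | 0.90 | 0.70 | 0.195 | 0.497 | −0.302 | −0.09 | −0.15 |

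**Effect on the test.** At the document rates the sets are 63 × 0.736 = 46.4 and 63 × 0.80 = 50.4 families. The standard error is √(1/46.4 + 1/50.4) = 0.203 SD, and the two-sided type I error becomes 5.2% (ρ = 0.3) to 5.6% (ρ = 0.5). If only 70% of IYP completers finish HPS (0.80 × 0.70 = 0.56 kept, 35.3 against 50.4 families), the bias is 0.11 to 0.18 SD and the type I error 7.7% to 12.7%.

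The two mechanisms act in opposite directions: the extra HPS requirement keeps more engaged HPS families, while better IYP retention keeps less engaged ones. The documents do not say which dominates.

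**The case against.** Every per-protocol set gives up randomisation, and this one is openly supplementary, in a pilot. The intention-to-treat analysis includes everyone, and non-completion is also summarised descriptively. The Discussion ties expansion of HPS to finding a significant effect size and does not mention the per-protocol set. At the document's own rates the bias is small beside the 0.57 SD detectable effect. All of this stands, and it limits the point to a cheap improvement. It does not rescue the stated purpose, which a set of compliers selected by unequal rules cannot serve.

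Three stronger readings are tempting and are not supported.

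- *That families who miss the 6-month visit are dropped from the post-treatment comparison.* The definition asks for relevant assessments at each time, which can equally mean those needed for each analysis. The wording needs settling, but the loss is not established.
- *That an instrumental-variable analysis gives an unbiased answer.* Two-stage least squares is consistent, not unbiased, and only if allocation acts solely through HPS. Parents know their arm (Blinding) and report the primary outcome. Group leaders also know it and collect the post-treatment ECBI (Post-treatment). The HPS package includes multidisciplinary review and access to specialist assessment beyond the home sessions.
- *That the bias flatters HPS.* Either sign is possible. If HPS raises IYP completion as hypothesised, the bias can run against it.

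**Conclusion.** The point holds as a minor one. The per-protocol set is selected after randomisation by a rule that differs between arms, on behaviour that HPS is expected to change, so its difference from the intention-to-treat result does not identify a compliance effect. That conclusion follows from the text and needs no assumed number.

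The size does rest on assumptions. It is about 0.03 to 0.05 SD at the document's 80% and 92%, assuming equal IYP completion, independence and ρ of 0.3 to 0.5. It reaches about 0.19 SD if only 55% of HPS families are kept, and is about −0.09 to −0.15 SD if HPS raises IYP completion from 70% to 90%. A reader might infer that the trial's main conclusion is compromised. It is not, because the intention-to-treat comparison does not use this set.

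**What to change.** 1. Label the per-protocol comparison descriptive and remove the statement that it identifies whether compliance affects outcomes.
2. State that the post-treatment per-protocol comparison needs only baseline and post-treatment data.
3. For uptake of HPS, add a complier-average causal effect in all randomised families. Use randomised arm as the instrument and a prespecified HPS exposure: either completion, or sessions received (0 to 10) with linearity stated as an assumption. Adjust for baseline ECBI and strata, and use multiple imputation for missing outcomes. Confirm from the records that controls received no HPS.
4. State its limits: it assumes that allocation acts only through HPS, which unblinded parent report and the wider HPS package may strain, and it says nothing about compliance with IYP.

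The cost is one extra model and a few reworded lines. HPS sessions are already recorded (Intervention fidelity) and compliance is already to be captured. The confidence interval will be wider. With no HPS in controls and a binary exposure, the unadjusted estimate is the intention-to-treat difference divided by the share exposed. At an illustrative share of 0.736, both estimate and interval grow by about 1 / 0.736 = 1.36. The model therefore rescales the randomised evidence to those who took up HPS and adds little new evidence on whether HPS works.
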